### **6.3 End-of-treatment visit**

The end-of-treatment visit is considered to be within 8 weeks after the end of the study. If the subject starts the follow-up anti-tumor treatment within this period, the end-of-treatment visit should be completed before then.

1. Vital signs.
2. Physical examination.
3. ECOG score.
4. Laboratory examination.
5. Histopathological test (if clinically required).
6. 12-lead electrocardiogram.
7. Cardiac ultrasound examination (including evaluation of left ventricular ejection function).
8. Thyroid function: Evaluated every 3 weeks ( $\pm 3$  days) from the first administration.
9. Pulmonary function: Evaluated every 12 weeks ( $\pm 7$  days) from the first administration or there may be clinical needs.
10. Serum pregnancy test (if applicable).
11. Bone marrow examination (smear  $\pm$  biopsy): for bone marrow infiltration or there may be clinical needs.
12. Tumor evaluation.
13. Record the combined medication.
14. Record AE.

## **6.4 Follow-up of progression-free survival**

Starting from 8 weeks after the last administration of the study drug, patients with stable or improving condition or those with early termination due to intolerance will be followed up for progression-free survival every 12 weeks ( $\pm 7$  days). Radiological examinations will be carried out until disease progression, death, withdrawal of ICF, start of other new treatments or end of the entire study (whichever occurs first).

## **6.5 Follow-up of overall survival**

For patients who have already progressed and started other new treatments, survival follow-up will be carried out every 8 weeks ( $\pm 7$  days) and the following anti-tumor treatment information and survival data of the patients will be collected until 2 years after the first administration.

# **7 Response assessments**

## **7.1 Outcome measures**

### **7.1.1 Primary outcome measures**

1. Responses were defined according to RECIL 2017 Response Criteria for Malignant Lymphoma including Objective Response Rate (ORR), Complete Remission Rate (CRR), Partial Remission Rate (PRR).
2. MTD of Chidamide: Maximum tolerable dose of chidamide among participants.
3. DLT of Chidamide: Dose-limiting toxicities of chidamide among participants.
4. RP2D of Chidamide: Recommended phase II dose (RP2D) of chidamide among participants.

### **7.1.2 Secondary outcome measures**

1. Progression-Free Survival (PFS) time.

2. Duration of Response (DoR).
3. DoR: Among participants who experience an objective response, DoR is defined as the date of their first objective response (which is subsequently confirmed) to disease progression or among participants who experience an objective response.
4. Overall survival refers to the time from the beginning of randomization to death due to any reason.
5. The frequency and severity of adverse events (Adverse Event, AE) and the frequency of severe adverse events (Severe Adverse Event, SAE) (CTCAE v5.0).
6. To Explore biomarkers that may have predictive effects.

## **7.2 Evaluation of efficacy**

The efficacy of the study drug will be determined by the objective tumor evaluation made by the research center based on the RECIL 2017 Response Criteria for Malignant Lymphoma.

Radiological evaluation of tumor is determined by PET/CT, MR or CT with uniformity in evaluation method as well as machine and technical parameters throughout the study period. Unless contraindications, contrast agents should be used. The radiological results are interpreted by researchers or radiologists in each research center. If the tumor evaluation has been performed within 21 days before enrollment with the same method and machine in the same hospital, it can be used as a baseline tumor evaluation. The baseline tumor evaluation should include the nasal cavity, chest, abdomen, pelvis and any other suspected areas. If there are clinical indications, appropriate methods, such as cranial MRI, bone scan can be used to examine any other known or suspected disease sites.

From the day of the first administration, radiological examination will be performed to evaluate the tumor condition every 6 weeks (-7 days) until the completion of 6 cycles of treatment, PD, intolerable toxicity, death, investigator's decision or patient's voluntary withdrawal from the study (whichever occurs first). Repeated every 8 weeks after 6 cycles up to 12 months, or disease progression, intolerable toxicity, death, investigators' decision, or the patient's voluntary withdrawal from the study. Researchers can arrange additional radiological examinations based on the patient's clinical conditions. If the medication is suspended due to AE or other reasons, the tumor evaluation will still be carried out as originally planned. For patients who are suspected of developing PD before the next scheduled tumor evaluation, an unscheduled tumor evaluation should be performed.

## **8 Safety assessment**

### **8.1 Safety Endpoint**

Safety monitoring begins when the ICF is signed and continues until 4 weeks after the end of treatment or until the beginning of another anti-tumor treatment (whichever occurs first). The safety endpoints of this study are as follows:

- The incidence, type and severity of adverse events during treatment are classified according to NCI-CTCAE (version 5.0). Research-related TEAE, SAE, Grade 3 or higher non-hematological AE, Grade 4 hematological AE and permanent discontinuation due to TEAE.
- The frequency and causes of deaths that occurred within 4 weeks ( $\pm 3$  days) of the last medication.
- Safety laboratory inspections classified according to NCI-CTCAE (version 5.0).
- Vital signs, ECG, full physical examination and ECOG physical status score.

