| Bone marrow aspiration and biopsy  | × |   |   |   |   |   | × |   |   |  |
| Biomarker collection                            |   |   |   |   |   |   |   |   |   |  |
| Peripheral blood                   | × | × | × | × | × | × | × |   |   |  |

Note.

- End of treatment (EOT): the date of termination of study treatment is defined as the date on which the investigators confirms that the subject needs to terminate the study treatment for any reason. The time window of termination of study treatment visit is +28 days.
- Safety follow-up: the time window of safety follow-up was 30 days after the last study  $\pm$  3 days; If the study treatment termination visit occurs within the time window of safety follow-up, the same examination items need not be repeated.
- Radiography follow-up: except for the subjects who stopped taking drugs due to the judgment of disease progression according to imaging evaluation, the imaging evaluation was continued according to the established time until the occurrence of imaging disease progression, the start of new anti-tumor treatment, withdrawal of informed consent, death or the end of the study (whichever occurs first)
- Survival follow-up: after the last study, the survival of the subjects was followed up by telephone every 12 weeks, and the survival of the patients with disease progression was followed up every 8 weeks.
- Combined use of drugs: The combined medication within 30 days before the screening visit was recorded until the safety follow-up was completed.
- Adverse events: all AE were recorded from the signing of informed consent until 30 days after the last study treatment; SAE should be recorded until 90 days after the last study treatment or the start of new anti-tumor treatment, whichever occurs first. After that, only SAE related to the study treatment should be recorded.
- ECG: ECG will be in screening period, treatment period (3 weeks)  $\pm$  3 days) and safety follow-up, ECG examination can be added if necessary.
- Height, weight and vital signs: height examination was only carried out in the screening period, weight examination was only carried out in the screening period, study treatment termination visit and safety follow-up; Vital signs include body temperature, pulse rate, respiratory rate and blood pressure.

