## 8.2 Evaluation of Adverse Events

### 8.2.1 Definition of adverse events

Adverse events refer to any adverse medical events that occur after exposure to a drug (including research drugs) while not necessarily have a causal relationship with the treatment. Therefore, AE can be any unfavorable and unexpected signs (including abnormal laboratory test results), symptoms or diseases temporally correlated to medication regardless of whether it is causally related to the treatment.

Adverse events during treatment refer to AEs that occurred after the first administration of research drugs.

**Note:** AE can therefore refer to any unfavorable and unexpected signs (including abnormal laboratory test results), symptoms or diseases (new or worsening) temporally correlated to medication. For marketed drugs, it also includes failure to obtain the expected benefits, abuse or misuse.

Events that meet the AE definition include:

1. Exacerbation of pre-existing chronic or intermittent diseases, including increased frequency and/or severity.
2. A newly discovered or diagnosed disease after the trial treatment, although the disease may have existed before the start of the study.
3. Suspected signs, symptoms or clinical sequelae of drug interactions.
4. Suspected signs, symptoms or clinical sequelae of trial treatment or concomitant overdose (overdose itself will not be reported as AE/SAE).
5. "Lack of efficacy" or "failure to achieve the expected pharmacological effect" itself is not reported as an AE or SAE. However, any signs and symptoms and/or clinical sequelae caused by "lack of efficacy" will be reported as an AE or SAE if they meet the corresponding definition.

Events that do not meet the definition of AE include:

1. Internal medicine or surgery (for example, endoscopy and appendectomy) while the conditions leading to the above surgery are determined as AEs.
2. The absence of adverse medical events (social and/or environmental facilitating admission).
3. Pre-existing disease or condition at the beginning of the study, with predictable fluctuations that did not aggravate during the study period.
4. The studied disease/abnormality or the expected progression, signs or symptoms of the disease/abnormality under study, unless it is more severe than expected.
5. The collection of AE should start from signing the informed consent form until 30 days after the medication.

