### **8.2.2 Definition of serious adverse events**

Serious adverse events were the following AEs at any dose:

- a) Results in death.
- b) Life threatening.
- c) Note: The term "life-threatening" in the definition of "serious" means that the patient is at risk of death when the event occurs, and does not mean death if the event is more serious.
- d) Need to be hospitalized or extend the length of hospitalization.

**Note:** Generally speaking, hospitalization refers to patients staying in a hospital or emergency ward (generally at least overnight) and/or receiving treatment that is not suitable for conduction in doctor's office or outpatient department. Complications that occurred during hospitalization were AEs. If the complication prolongs the hospital time or meets any other serious criteria, the event is an SAE. When it is uncertain whether it should be "hospitalized" or required for "hospitalization", the AE

should also be regarded as an SAE.

Hospitalization due to selective treatment or pre-existing disease that has not worsened than baseline is not an AE.

- e) Results in disability/dysfunction.

**Note:** The term “disability” refers to severe influence of an individual’s ability to conduct normal life functions. This definition does not include events of relatively little clinical significance, such as simple headaches, nausea, vomiting, diarrhea, flu and accidental trauma (such as ankle sprains), which may affect daily function but dose not cause significant loss of function.

- f) Congenital malformations/birth defects.
- g) In other cases, medical or scientific judgment is required to determine whether to report. For example, it may not immediately threaten life or cause death or hospitalization, but it may threaten the patient or may require medical or surgical intervention to prevent the other important medical events listed in the above definition. These should also be considered SAEs, such as invasive or malignant tumors, allergic bronchospasm with intensive treatment in the emergency room or at home, blood disorders, convulsions that did not lead to hospitalization or drug dependence/abuse.

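### Section 8.1 stops safety monitoring, SAEs included, at 4 weeks, while the flow-chart note records SAEs to 90 days and related SAEs beyond, so SAE frequency depends on the section followed

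*Protocol*

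**What the plan says.** Three places in the current protocol text set an end to safety collection.

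- **Section 8.1 (Safety Endpoint)** sets one limit for all safety monitoring: it "continues until 4 weeks after the end of treatment", or stops when other anti-tumor therapy starts, whichever is first. The same section then lists the endpoints, among them "Research-related TEAE, SAE, Grade 3 or higher non-hematological AE".
- **Section 8.2.1 (Definition of adverse events)**, last item: "The collection of AE should start from signing the informed consent form until 30 days after the medication". It has no separate rule for SAEs and no cut at new therapy. Section 8.2.2 defines SAEs as a subset of AEs: "Serious adverse events were the following AEs at any dose".
- **Study flow chart, note on adverse events**: "all AE were recorded from the signing of informed consent until 30 days after the last study treatment". For serious events, "SAE should be recorded until 90 days after the last study treatment or the start of new anti-tumor treatment, whichever occurs first". It adds: "After that, only SAE related to the study treatment should be recorded", and gives no end date for that last rule.

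The frequency of SAEs is a secondary endpoint (synopsis, section 2 and section 7.1.2). None of those entries gives a window. Section 10.3, which describes the safety summaries, gives none either, and the definition of treatment-emergent events in 8.2.1 has a start but no end.

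**The concern.** The section that defines the safety endpoints has the shorter limit, and the only rule written specifically for SAEs has the longer one. A coordinator who takes 8.1 at its word may close safety collection at week 4. A coordinator who works from the flow chart keeps recording SAEs to day 90, and related ones after that. Both would be following the protocol.

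At stake is the SAE count for a new combination that includes an immune checkpoint inhibitor, in a multicenter study whose phase 2 part has 28 patients. In a group of that size a few unrecorded events would visibly change the rate. The loss could also not be repaired at analysis: an analysis plan can choose which recorded events to count, but it cannot bring back events that a site never recorded.

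**Working it through.** The protocol gives no figure to reproduce, so the check sets the rules side by side, taking 4 weeks as 28 days.

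| Place | Covers | Length | Clock starts at | Effect of new anti-tumor therapy |
|---|---|---|---|---|
| 8.1 | all safety monitoring, SAEs named as an endpoint | 28 days | end of treatment | ends everything |
| 8.2.1 | AEs, SAEs not separated | 30 days | the medication | none stated |
| Flow-chart note, AEs | all AEs | 30 days | last study treatment | none stated |
| Flow-chart note, SAEs | SAEs | 90 days, then related SAEs only | last study treatment | ends recording of unrelated SAEs, related ones continue |

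**Non-serious AEs.** 8.2.1 and the flow chart agree at 30 days. Section 8.1 differs by 30 − 28 = 2 days, which lies within the ±3 days allowed for the 30-day safety visit. Its different start date and its cut at new therapy remain, but the length itself is a minor matter.

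**SAEs, both clocks starting on the same day, no new therapy before day 90.** The flow chart covers 90 − 28 = 62 days (days 29 to 90) that 8.1 does not. If 8.2.1 is read as covering SAEs too, the difference from the flow chart is 90 − 30 = 60 days.

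**Effect of different clocks.** The flow-chart notes define the end-of-treatment date as the day on which the investigator confirms that treatment must stop, not the day of the last dose. If that confirmation comes *d* days after the last study treatment, 8.1 closes at day 28 + *d* on the flow chart's clock, and the gap is 90 − (28 + *d*) = 62 − *d* days. The protocol does not bound *d*. Two interruption limits in the text show the range:

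- *d* = 0: gap 62 days
- *d* = 28 (the 4-week interruption limit in 3.1): gap 62 − 28 = 34 days
- *d* = 84 (the 12-week limit for suspending sintilimab in 5.5, if no study drug is taken meanwhile): 62 − 84 = −22, so 8.1 would close 22 days after the flow chart's day 90

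**Effect of new therapy.** With *d* = 0 and new therapy on day *t*, both windows for unrelated SAEs close at *t* if *t* is 28 or less, so the gap is 0. For *t* between 28 and 90 the gap is *t* − 28 days. Related SAEs behave differently: the flow chart goes on recording them after new therapy starts, while 8.1 has already closed.

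So 62 days is the upper end of the gap up to day 90. Related SAEs after day 90 come on top of it and have no stated limit.

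**The case against.** Four arguments weigh against the point.

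1. *Section 8.2.1 does not conflict with the flow chart.* A 30-day rule for AEs beside a longer rule for SAEs is a natural reading. This stands. A reader might infer a three-way conflict, but for non-serious AEs the two places agree. What 8.2.1 lacks is any mention of an SAE extension.
2. *Both rules can be met.* Section 8.1 speaks of monitoring and forbids no later recording, and a site recording to day 90 holds everything that 8.1 needs. This is correct for such a site, so it would be too strong to say that the rules are mutually exclusive. It does not help with a site that stops at week 4, as 8.1 allows, and it leaves open which events the endpoint counts.
3. *Section 8.2.7 looks past follow-up.* It requires every SAE to be reported within 24 hours and, in garbled wording, contemplates reporting after the follow-up period ends. This makes it less likely that a site would stop at week 4. It also means that section 8 does not agree with itself, and 8.2.7 gives no window.
4. *The size is easily overstated.* Since 62/90 = 69%, a reader might infer that 69% of post-treatment SAEs would be lost. The documents do not support that. It is a share of calendar time, not of events, and a maximum, because the clocks start on different days and early new therapy shortens both windows. Patients with stable or progressive disease leave treatment (section 5.1) and may start new therapy early.

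**Conclusion.** The inconsistency is real. It stands between 8.1 and the SAE rule in the flow-chart note, and nothing in the endpoint definitions or in 10.3 resolves it. A site that follows 8.1 could omit SAEs from about week 4 to day 90, at most about 62 days per patient, and related SAEs that arise after new therapy starts. The 62 days assume that the last study treatment and the end-of-treatment date coincide and that no new therapy starts before day 90. The number of events affected cannot be derived from the documents.

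The point concerns the SAE frequency endpoint. It is not shown to touch response rate or the dose-finding objectives. A reader might also infer that the documents prove the 90-day window to be the intended one. They do not. The flow-chart note is the natural candidate because it is the only SAE-specific rule, but the sponsor has to confirm it.

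**What to change.** Reconcile 8.1, 8.2.1 and the flow-chart note so that they state the same three things for SAEs:

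- one window length, including what happens to related SAEs afterwards;
- one anchor date, either the last dose or the end-of-treatment date;
- one rule for the start of new anti-tumor therapy.

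Name that window in 10.3 as the one used for the SAE summaries. If the flow-chart rule is confirmed, 8.1 needs its SAE limit changed, and 8.2.1 can keep its 30 days for AEs with one added sentence or cross-reference for SAEs.

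The cost is small but not wording alone. It would be easy to assume that the schedule already plans collection to day 90, but the adverse-event row of the flow chart is ticked only as far as the 30-day safety visit, and the longer window appears only in the note. If 90 days is kept, an SAE query, with onset date, should be added to the existing 12-week follow-up contact. That contact falls at 12 × 7 = 84 days, ±7, that is days 77 to 91, so the following contact should ask about any days left up to day 90. No new visit is needed.

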## 8.2 Evaluation of Adverse Events

### 8.2.1 Definition of adverse events

Adverse events refer to any adverse medical events that occur after exposure to a drug (including research drugs) while not necessarily have a causal relationship with the treatment. Therefore, AE can be any unfavorable and unexpected signs (including abnormal laboratory test results), symptoms or diseases temporally correlated to medication regardless of whether it is causally related to the treatment.

Adverse events during treatment refer to AEs that occurred after the first administration of research drugs.

**Note:** AE can therefore refer to any unfavorable and unexpected signs (including abnormal laboratory test results), symptoms or diseases (new or worsening) temporally correlated to medication. For marketed drugs, it also includes failure to obtain the expected benefits, abuse or misuse.

Events that meet the AE definition include:

1. Exacerbation of pre-existing chronic or intermittent diseases, including increased frequency and/or severity.
2. A newly discovered or diagnosed disease after the trial treatment, although the disease may have existed before the start of the study.
3. Suspected signs, symptoms or clinical sequelae of drug interactions.
4. Suspected signs, symptoms or clinical sequelae of trial treatment or concomitant overdose (overdose itself will not be reported as AE/SAE).
5. "Lack of efficacy" or "failure to achieve the expected pharmacological effect" itself is not reported as an AE or SAE. However, any signs and symptoms and/or clinical sequelae caused by "lack of efficacy" will be reported as an AE or SAE if they meet the corresponding definition.

Events that do not meet the definition of AE include:

1. Internal medicine or surgery (for example, endoscopy and appendectomy) while the conditions leading to the above surgery are determined as AEs.
2. The absence of adverse medical events (social and/or environmental facilitating admission).
3. Pre-existing disease or condition at the beginning of the study, with predictable fluctuations that did not aggravate during the study period.
4. The studied disease/abnormality or the expected progression, signs or symptoms of the disease/abnormality under study, unless it is more severe than expected.
5. The collection of AE should start from signing the informed consent form until 30 days after the medication.

### **8.2.2 Definition of serious adverse events**

Serious adverse events were the following AEs at any dose:

- a) Results in death.
- b) Life threatening.
- c) Note: The term "life-threatening" in the definition of "serious" means that the patient is at risk of death when the event occurs, and does not mean death if the event is more serious.
- d) Need to be hospitalized or extend the length of hospitalization.

**Note:** Generally speaking, hospitalization refers to patients staying in a hospital or emergency ward (generally at least overnight) and/or receiving treatment that is not suitable for conduction in doctor's office or outpatient department. Complications that occurred during hospitalization were AEs. If the complication prolongs the hospital time or meets any other serious criteria, the event is an SAE. When it is uncertain whether it should be "hospitalized" or required for "hospitalization", the AE

should also be regarded as an SAE.

Hospitalization due to selective treatment or pre-existing disease that has not worsened than baseline is not an AE.

- e) Results in disability/dysfunction.

**Note:** The term “disability” refers to severe influence of an individual’s ability to conduct normal life functions. This definition does not include events of relatively little clinical significance, such as simple headaches, nausea, vomiting, diarrhea, flu and accidental trauma (such as ankle sprains), which may affect daily function but dose not cause significant loss of function.

- f) Congenital malformations/birth defects.
- g) In other cases, medical or scientific judgment is required to determine whether to report. For example, it may not immediately threaten life or cause death or hospitalization, but it may threaten the patient or may require medical or surgical intervention to prevent the other important medical events listed in the above definition. These should also be considered SAEs, such as invasive or malignant tumors, allergic bronchospasm with intensive treatment in the emergency room or at home, blood disorders, convulsions that did not lead to hospitalization or drug dependence/abuse.

